## Abstract

**Background:**

Poststroke aphasia (PSA) is a disabling condition that decreases the quality of life, and the duration of the disease harms the quality of life of PSA patients. Acupuncture has been widely employed for PSA. There is some evidence for the immediate treatment efficacy of acupuncture for PSA; however, long-term results after acupuncture may be poorer.

**Methods:**

This is a multicentre, randomized, blinded, nonacupoint (NA) acupuncture controlled, multimodal neuroimaging clinical trial. A total of 48 subjects with subacute PSA will be randomly assigned to an acupoint group or an NA control group. The acupoint group will receive acupuncture with normal needling at DU20, EX-HN1, HT5, GB39, EX-HN12, EX-HN13, and CV23. The NA control group will receive acupuncture in locations not corresponding to acupuncture points as sham acupoints. Both groups will receive identical speech and language therapy thrice a week for four weeks. The primary outcome will be the change in the aphasia quotient (AQ) score measured by the Western Aphasia Battery (WAB) test during the 12th week after randomization. Participants will be blindly assessed at prerandomization (baseline) and 4 weeks, 12 weeks, and 24 weeks after randomization. The secondary outcomes include the Boston Diagnostic Aphasia Examination (BDAE) score, the Disease Prognosis Scale score for ischaemic stroke, etc. Magnetic resonance imaging (MRI) and electroencephalogram (EEG) will also be performed at 4-time intervals as secondary outcomes. All scores and image evaluations will be taken at the same point as the linguistic evaluation. The multilevel evaluation technique will be used to assess the long-term efficacy of acupuncture therapy. MRI scans and EEG will be used to assess acupuncture-related neuroplasticity changes. *Discussion*. The results from our trial will help to supply evidence for the long-term acupuncture effects for PSA over a long follow-up period. It will provide valuable information for future studies in the field of PSA treatment. The trial was registered at the Chinese Clinical Trial Registry on 16 March 2020 (ChiCTR2000030879).

## 1. Introduction

Stroke is a leading cause of mortality and disability globally [1]. Poststroke aphasia (PSA) is one of the most devastating symptoms in stroke survivors [2], who rarely spontaneously recover in the ensuing time. Approximately 30% of stroke patients suffer from aphasia [3], 50% of stroke survivors are still aphasic one year after stroke, and residual symptoms may persist for many years [4]. It can impact an individual's ability to speak, comprehend spoken language, read, and write [5]. Basic requirements of daily life that rely on communication are affected, and social participation can be dramatically impaired. A large-scale survey investigated the relationship between the presence or absence of 75 diseases and the quality of life scores. The highest negative correlation is aphasia [6]. Aphasia rehabilitation has been listed as one of the top 10 research priorities related to life after aphasia [2]. Patients with PSA experience longer hospitalization stays and need more healthcare support, so studying the long-term curative effect of acupuncture treatment on PSA is conducive to maximizing of medical resources.

A review of clinical trials for PSA over the past 5 years revealed that a multitude of interventions can be beneficial in improving language and functional outcomes for patients with PSA [5], with the majority of high-quality clinical research focusing on the chronic phase of aphasia [7–9]. Language disorders are diverse and can change over time. The clinical symptoms may be different in the subacute phase as well as in the chronic phase [10]. Only a few randomized studies (*n* = 12–30) have examined the efficacy of PSA treatment in the subacute phase [11–13]. Research on the subacute period is therefore relatively scarce.

Effective therapies focusing on improving speech and language in patients with PSA are essential. At present, considerable evidence has suggested that treatment with speech and language therapy (SLT) is effective in improving communication and quality of life in individuals with aphasia. These studies have provided evidence of the effectiveness of SLT for people with aphasia following stroke in terms of improved functional communication, reading, writing, and expressive language compared with no therapy [14]; however, the effect sizes of SLT are moderate, potentially reflecting a physiological limit of training-induced progress, the treatment is costly, and progress is often slow. One of the studies also stated that SLT for more than 2 hours a day provided no added value on PSA [15]. It is certain that the various stages of PSA are associated with varying degrees of language recovery, but recovery requires a large number of therapy sessions. It remains a challenge to optimize the effect of aphasia therapy. As a result, an increasing amount of research has been devoted to alternative methods to improve the effectiveness of aphasia treatment, generally by increasing the total amount of treatment achieved [16].

Acupuncture is an easy-to-use, low-cost adjunct to traditional SLT to enhance language outcomes in individuals with PSA. It is one of the main treatments of traditional Chinese medicine (TCM) and has been used for thousands of years. During the past decade, the results of several meta-analyses have concluded that acupuncture after stroke seems to be effective in improving PSA functional communication and language function [17, 18]; however, most of the studies did not assess therapeutic effects over extended periods. For acupuncture treatment, long-term efficacy is considered one of the most important therapeutic effects, which has been suggested by numerous clinical studies [19–25]. It represents the cumulative effect of positive achievements [16]. Long-term efficacy will allow the patient's therapeutic effects to accumulate (“more is better”). Our previous studies on the effects of acupuncture on PSA have shown that participants in the acupuncture group had lower severity than the control group in week 4, but the difference was not significant; however, a significant reduction in PSA severity during weeks 5 to 12 was noted [26]. In addition, we explored the traditional Chinese medical theory and acupuncture technique of this acupuncture programme [27, 28]. Acupuncture has also been shown to have long-term efficacy in chronic pain and tinnitus, which has shown effective therapeutic results [29, 30]. Therefore, we speculate that the long-term therapeutic effect for PSA will also be well maintained; however, the long-term efficacy of acupuncture compared with the placebo effect in patients with PSA has not been investigated.

In terms of the current state of evaluation of aphasia, the requirements for a comprehensive evaluation of PSA have not yet been fully implemented. One of the important means was to evaluate the language characteristics of PSA, which is the major part of the evaluation; however, to date, this single evaluation approach is often insufficient. As such, neuropsychological tests in conjunction with in vivo measures may be more sensitive than neuropsychological tests alone in the assessment of brain structure and electrophysiology [31–33]. We introduce MRI and EEG for evaluation of the objective characteristics of PSA because the multimodal assessment of brain structure and function allows for a more objective evaluation of the recovery characteristics of patients with aphasia. Based on the previous study [34], we conducted a TCM syndrome evaluation of PSA patients and confirmed the relationship between linguistic features and TCM syndrome. Therefore, in this study, we have also introduced the evaluation of TCM syndrome to provide more comprehensive evidence of efficacy based on the combined evaluation of Chinese and Western medicine. For the reasons above, we propose to investigate whether acupuncture treatment on PSA has the value of maintaining long-term efficacy through this randomized controlled trial (RCT) with multimodal evaluation.

We designed an assessor- and participant-blinded RCT with PSA patients. Using NA acupuncture as a control, the trial aims to identify the efficacy of acupuncture by answering two questions: (1) what is the long-term efficacy and reliability of acupuncture as an intervention for PSA compared with the placebo effect? and (2) what interactions will be observed through an integrated evaluation of linguistic features, brain function, and TCM syndrome?

## 2. Methods and Analysis

### 2.1. Study Design

This is a multicentre, randomized, assessor- and participant-blinded, NA acupuncture controlled, multimodal neuroimaging clinical trial. It aims to compare the long-term efficacy of the acupoint group and NA control group (in locations not corresponding to acupuncture points). In all groups, participants will receive identical SLT but will be permitted to use medications for the basic internal medicine treatment of stroke. The type, dose, and time of administration of the agent will be recorded in the case report form. The trial design is depicted by the flow diagram in Figure 1. The timeline for study enrolment, intervention, and assessment is illustrated in Table 1. We designed this acupuncture research at full length following the Standard Protocol Items: Recommendations for Interventional Trials (SPIRIT) 2013 statement [35]. The design and reporting of the study will follow the Consolidated Standards of Reporting Trials (CONSORT) statement for nonpharmacological interventions [36] (http://www.consort-statement.org/home/).

### 2.2. Randomization and Blinding

Eligible patients will be randomly assigned to the acupoint group or NA control group with a 1 : 1 ratio. The randomization sequence will be generated by a third-party professional statistician using a computer-generated randomization digital table using SAS V.9.4 software (SAS Institute Inc., North Carolina, USA). An independent assessor will interview the participants and carry out the screening. Random numbers and group assignments will be confirmed immediately through short message service to the practitioners who conduct acupuncture. All participants will be blinded to the types of acupuncture. An independent, blinded assessor who does not know the group assignment will conduct the outcome evaluation after the treatment. The researcher who will oversee the statistical analysis will also be blinded, with the treatment for each group remaining unknown; however, it is impossible to blind practitioners who conduct acupuncture. The practitioner will be forbidden from discussing the type of acupuncture with the participants. We will endeavour to ensure that subjects begin the trial with similar expectations of efficacy by informing them that the provided treatments are effective. In this study, participants, assessors, and statisticians will be blinded to treatment allocation. Participants will receive treatments alone at different times to avoid communication with each other. An eye patch will be applied to patients during the acupuncture treatment. To minimize the unintentional physical cues and bias in this trial, acupuncturists will be required to emulate the same procedure for the nonacupoint control group. In addition, participants will be asked to answer the following question during week 4 to test the blinding effect: “Do you think you have received real acupuncture treatment?” The participants can choose “yes” or “no” as an answer [37, 38]. The percentage of participants who answered “yes” in both groups after the final treatment will be analyzed. If the results show no significant difference in the response to this question between the two groups, they could suggest that the blinding effect is sufficient.

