#### 2.5.2. NA Control Group

Participants in the NA control group will receive sham acupuncture with real needles on an NA. NA 1 will be 0.5 cun (≈10 mm) lateral to HT5. NA 2 will be 0.5 cun (≈10 mm) horizontal to GB39, and NA 3 will be 0.5 cun (≈10 mm) lateral to ST8 (for details, see Table 5 and Figure 3). Procedures and other treatment settings will be the same as in the acupoint group but with no needle manipulation for de qi. In both groups, the needles will be retained for 30 minutes for each treatment session. The participants will be treated with acupuncture three times a week, on alternate days, for 4 successive weeks, resulting in a total of 12 sessions for each patient.

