Regarding the study design, we developed an assessor- and participant-blinded design to minimize bias. The specific effects are thought to be generated by needling the acupoint with the appropriate manipulation. The nonspecific effects are due to other aspects of the therapy, such as the expectations of the patient, which might influence the treatment outcome. To recognize the specific effects, a placebo is needed. Among acupuncture research, placebo controls for acupuncture studies have been difficult to select. To maximally exclude the placebo effect, rigorous methodological designs are followed. In our study, control conditions involve being punctured with real acupuncture needles at NA locations. Thus, the self-perception of placebo effects in the NA control group is difficult to distinguish from the real acupoints. Additional needle manipulations will not be used in the NA control group. De qi is a characteristic constellation of sensations felt by patients during acupuncture needling. It has been regarded as an important factor related to clinical effects; however, we do not pursue this kind of sensation in the NA control group. By following these methods, participants can be successfully blinded, and the efficacy of acupuncture could be confirmed if the results of the acupoint group prove superior to those of the NA control group.

We will assess patients with PSA on multiple levels, including multiple neuropsychological tests, functional and structural brain alterations, and TCM syndrome evaluation. This multidomain assessment will be used to identify possible biomarkers involved in the effects of acupuncture in PSA.

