	(6b) Precise description of the control or comparator; details for items 1–3 with the use of sham acupuncture or any other type of acupuncture-like control	Participants in the nonacupoint control group received sham acupuncture with a pragmatic placebo needle on a sham acupoint. The needles used are the same as the acupoint group. Procedures and other treatment settings will be the same as in the acupoint group but with no needle manipulation for de qi

**Table 4 tab4:** Location of acupoints used in the acupuncture group.

Acupoints	Location
DU20 (Baihui)	On the median line of the head, 5 cun superior to the anterior hairline, at about the middle on the connecting line between the two auricular tips
EX-HN1 (Sishencong)	On the vertex, 1 cun from the front, back, left, and right to DU20 (Baihui), common 4 points
HT5 (Tongli)	On the palmar side of the forearm, 1 cun superior to the transverse crease of the wrist, at the radial border of the ulnar carpal flexor muscular tendon
GB39 (Xuanzhong)	On the lateral side of the leg, 3 cun directly above the tip of lateral malleolus at the anterior border of the fibula
EX-HN12 (Jinjin)	In the mouth, EX-HN12 (Jinjin) is located with tongue furled, on the vein on the left side of the frenulum of the tongue
EX-HN13 (Yuye)	EX-HN13 (Yuye) is located on the vein on the right side of the frenulum of the tongue
CV23 (Lianquan)	In the neck, on the anterior midline, above the laryngeal protuberance, in the depression of the superior border of the hyoid bone

**Table 5 tab5:** Location of sham acupoints used in the NA group.

Nonacupoint (NA)	Location
NA 1	0.5 cun lateral to HT5 (Tongli)
NA 2	0.5 cun horizontal to GB39 (Xuanzhong)
NA 3	0.5 cun lateral to ST8 (Touwei)

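### The blinding question asks about 'real acupuncture' although controls are also needled with real needles, so similar yes rates are only weak evidence that allocation was hidden

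*Protocol article*

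**What the plan says.** Section 2.2 (Randomization and Blinding) sets out the check. Participants are asked in week 4: "Do you think you have received real acupuncture treatment". The format is binary: "The participants can choose “yes” or “no” as an answer". The summary measure is the yes percentage: "The percentage of participants who answered “yes” in both groups after the final treatment will be analyzed". The reading rule treats a null result as reassurance: "If the results show no significant difference in the response to this question between the two groups, they could suggest that the blinding effect is" (the sentence ends by calling it sufficient). The same section says that what is concealed from participants is the type of acupuncture, and that participants are told the treatments provided are effective.

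The control is an invasive one. Section 2.5.2: "Participants in the NA control group will receive sham acupuncture with real needles on an NA". The Discussion repeats that "control conditions involve being punctured with real acupuncture needles at NA locations". Table 3 (STRICTA), item 6b, adds: "The needles used are the same as the acupoint group". That item also uses the term placebo needle, which sits badly with its own next sentence, but section 2.5.2 and the Discussion are clear that the needles are real. The arms differ in the sites needled, in the manipulation for de qi, and in the tongue bloodletting and neck point that section 2.5.1 describes for the acupoint arm only.

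**The concern.** A blinding check should ask about the thing that is hidden. Here that is the type of needling: acupoints with manipulation, or other sites without it. The item asks instead whether the treatment was real acupuncture. Taken literally, yes is a true answer in both arms, whatever the participant has worked out about allocation. With no 'don't know' option, a participant without an opinion must also choose a side.

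The distortion runs in one direction. Literal yes answers pull the two arms together, and the reading rule treats similarity as success. The first aim in the Introduction is efficacy compared with the placebo effect, and the Discussion says participants can be successfully blinded and that superiority over the control could confirm efficacy. This item is the only check of participant blinding that the article describes. If it understates a difference in belief, an expectation effect on the aphasia quotient could pass for an effect of the acupoints.

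**Working it through.** The protocol gives no expected yes rate, margin or power for the check, so there is no planned figure to reproduce.

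**Inputs from the protocol article.** 1:1 allocation (section 2.2); 20 analysed and 24 recruited per arm (section 2.6); two-sided 0.05 level and chi-square test for categorical data (section 2.9.1).

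**Assumptions, not in the protocol.** A proportion q believe they had the acupoint regimen: 0.85 in the acupoint arm and 0.45 in the control arm. Of those who believe they had the comparison regimen, a share L still answer yes because the needles were real.

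**Step 1, attenuation.** The observed yes rate is q + (1 − q)L, so the observed gap is (0.85 − 0.45)(1 − L) = 0.40(1 − L). For L = 0.5 the rates are 0.85 + 0.15 × 0.5 = 0.925 and 0.45 + 0.55 × 0.5 = 0.725, a gap of 20 points.

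**Step 2, chance that the test is significant.** Exact binomial enumeration of the uncorrected chi-square test:

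| L | Yes, acupoint | Yes, control | Gap (points) | 20 per arm | 24 per arm |
|---|---|---|---|---|---|
| 0 | 85.0% | 45.0% | 40 | 79.5% | 86.2% |
| 0.25 | 88.75% | 58.75% | 30 | 60.8% | 69.3% |
| 0.5 | 92.5% | 72.5% | 20 | 39.4% | 47.5% |
| 0.75 | 96.25% | 86.25% | 10 | 15.4% | 21.0% |
| 1 | 100% | 100% | 0 | 0% | 0% |

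The first row is the cost of the small sample alone. The fall below it is the cost of the wording.

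**Step 3, a different set of assumptions.** Let the acupoint arm answer yes at 95%, let a share u of controls know their arm, and let a share f of those answer literally. The control yes rate is 0.95 × (1 − u(1 − f)).

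- u = 1, f = 1: 95% in both arms; significant in 1.2% (20 per arm) to 1.8% (24 per arm) of trials, although every control knows.
- u = 1, f = 0.75: control rate 71.25%; significant in 55.5% to 65.1%.
- u = 0.5, f = 0: control rate 47.5%; significant in 96.1% to 98.5%.

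**Step 4, does sample size cure it?** With the inputs of step 1 and 100 per arm, the test is significant in 99.9%, 97.4% and 74.2% of trials for L = 0.25, 0.5 and 0.75; with 200 per arm and L = 0.75, in 95.7%. Detection recovers for any L below 1. The bias in the estimated gap does not: at L = 0.5 it stays at 20 points when the gap in belief is 40.

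**The case against.** The strongest reply is about meaning. The question concerns real acupuncture treatment, not real needles, and the protocol consistently calls the control sham. A participant who was told of a sham arm may well read 'real' as 'not sham' and answer no on suspecting it. L would then be near 0 and the item would work much as intended. What participants were told is not in the material at hand, so this cannot be settled, and it stands as a limit on the point.

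A reader might infer that the item fails at any sample size and with any test, or that equal yes rates carry no information. The protocol does not support that: step 4 shows that it holds only at L = 1. A reader might also infer that blinding is broken. It may be under strain, since bloodletting in the mouth and de qi manipulation are perceptible, but the protocol provides eye patches, separate sessions and emulated procedures, and outcome assessors are blinded. A weak check is not evidence of failure.

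Three further replies have some force. The article cites earlier work for the yes/no format; that shows precedent, not that the wording suits a control needled with real needles. The rule is hedged as something the results could suggest. And a short yes/no question suits people with motor aphasia, which bears on how a replacement is worded.

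**Conclusion.** The point holds as one of ambiguity and attenuation. The item does not ask about the concealed feature, so the difference in yes rates understates the difference in belief by an unknown factor 1 − L, and similar yes rates are weak evidence that allocation was hidden. Under the illustrative 85% and 45% beliefs, the chance of detecting the difference ranges from 79.5% (L = 0) to 0% (L = 1) at 20 per arm, and from 86.2% to 0% at 24 per arm. Those beliefs and L have no source in the protocol, so the figures show the range of possible loss and are not a forecast. The primary analysis is untouched; what is weakened is the support for reading a difference in aphasia quotient as more than expectation. The item should be changed, because the remedy is cheap.

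**What to change.** Replace the item with a short guess of allocation that suits people with aphasia. One form is a card with three choices to point to: 'treatment points', 'comparison points', 'don't know'. Word it consistently with the consent information, so that the question does not itself reveal an arm of which participants had not been told; this matters because it is asked before the week-12 primary outcome.

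Ask it once, after the final session. Bring Table 1, which appears to mark the blinding assessment in week 1, into line with section 2.2, which gives week 4.

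Report the three answers by arm, with an arm-specific blinding index (for example Bang's: correct minus incorrect guesses, divided by the number asked) and its 95% confidence interval. Drop the rule that a non-significant difference suggests sufficient blinding.

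The cost is one reworded question and one line of analysis. There are small downsides: fewer definite guesses, less comparability with earlier studies that used yes/no, and a slightly harder question for this population. The index will also be imprecise: with even guesses and no 'don't know' answers its standard error is 1/√n, so the 95% half-width is 1.96/√24 = 0.40 at 24 per arm and 1.96/√20 = 0.44 at 20. The interval makes that uncertainty visible, which the present rule does not.

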#### 2.5.1. Acupoint Group

Participants in the acupoint group will receive acupuncture at bilateral Tongli (HT5) and Xuanzhong (GB39) limb acupuncture points. After skin disinfection, acupuncture needles will be inserted through the skin and approximately 0.5 cun [≈10 mm] into the skin. Needle insertion will follow an angle of 90° in an inferomedial direction for the two points. Following needle insertion, small, equal manipulations of twirling and thrusting will be performed on all needles to reach de qi (a composite of sensations including numbness, distention, soreness, and heaviness that is an important indicator of successful acupuncture treatment), which is believed to be an essential component for acupuncture efficacy. The needles placed in HT5 and GB39 will be manually stimulated every 10 minutes. The acupuncture points on the head are Lianquan (RN23), Jinjin (EX-HN12), Yuye (EX-HN13), Baihui (DU20), and Sishencong (EX-HN1). For RN23, acupuncture needles will be inserted through the skin and approximately 1 cun [≈20 mm] into the skin. Following needle insertion, small, equal manipulations will be performed on the needles to reach numbness. EX-HN12 and EX-HN13 will be quickly inserted for bloodletting. DU20 and EX-HN1 will be inserted through the skin approximately 0.5 cun. Needle insertion will follow an angle of 15° in an inferomedial direction for the two points (for details, see Table 4 and Figure 2).

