### 2.9. Statistical Analysis

#### 2.9.1. Clinical Data Analysis

All statistical analyses will be performed by a statistician from the Clinical Evaluation and Analysis Centre of Dongzhimen Hospital affiliated to BUCM using Statistical Package for the Social Sciences (SPSS) V.22.0. The statistician will be blinded to the allocation of groups. The level of significance is established at *α* < 0.05 with a two-tailed test. The main objective is to compare the change in the AQ score at week 12 from baseline between the acupoint group and the NA control group. The null hypothesis is that the acupoint group will show the same change as the NA control group, while the alternative hypothesis is that the acupoint group shows a greater improvement. Categorical data will be represented by percentages, whereas continuous data will be represented by the average, standard deviation, median, minimum value, and maximum value. For comparison with the baseline, a *t*-test or nonparametric test will be used for continuous data and nonparametric tests for categorical data. For comparison of two independent samples, if the residuals are normally distributed, the analysis of covariance (ANCOVA) will be used for the primary outcome and subgroup analysis stratified by aphasia severity, *t*-tests for other continuous data, and chi-square tests for categorical data; if the residuals are non-normally distributed, a nonparametric test will be used for both the continuous and categorical data. The results of the intention-to-treat (ITT) analysis will be used to assess the validity of the study as a whole. The ITT analysis will collect data from all the participants in this trial, and for those lost to follow-up, the last observation carried forward method will be implemented.

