**Figure 4 fig4:**
[figure not shown]
MRI experimental paradigm and an illustrative diagram of the word-picture judgement task. For fMRI, there were 60 blocks. For ERP, 60 blocks. When presenting the task, the word is displayed in Chinese.

**Table 1 tab1:** Study design schedule.

Period	Screening and baseline	Treatment (w1–4)				Follow-up (w5–12)	Follow-up (w13–24)
Week (W)	W −1	W1	W2	W3	W4	W12	W24
Eligibility	×						
CT or MRI	×						
General information	×						
Physical examination	×				×	×	×
Medical history and demography	×						
Informed consent	×						
WAB		×			×	×	×
BDAE		×			×	×	×
Disease Prognosis Scale of ischaemic stroke		×			×	×	×
MRI (3D-T1, RS-fMRI, Task-fMRI, DTI)		×			×	×	×
EEG		×			×	×	×
ERP		×			×	×	×
Discomfort and acceptance of acupuncture		×	×	×	×	×	×
Assessment of blind method		×					
Adverse event			×	×	×	×	×
Compliance			×	×	×	×	×

CT, computed tomography; MRI, magnetic resonance imaging; WAB, Western Aphasia Battery; BDAE: Boston Diagnostic Aphasia Examination; RS-fMRI, resting-state functional magnetic resonance imaging; DTI, diffusion tensor imaging; EEG, electroencephalogram; ERP, event-related potentials.

**Table 2 tab2:** List of participating institutions and level of the institution.

Participating centre	Level of the institution
Dongzhimen Hospital Affiliated to Beijing University of Chinese Medicine	Tertiary A hospital
China Rehabilitation Research Center	Tertiary A hospital
Peking University Third Hospital	Tertiary A hospital

**Table 3 tab3:** Revised standards for reporting intervention in clinical trials of acupuncture (STRICTA [39]]).

Item	Item criteria	Description
(1) Acupuncture rationale	(1a) Style of acupuncture	Traditional Chinese medicine therapy
	(1b) Reasoning for treatment provided, based on historical context, literature sources, and/or consensus methods, with references where appropriate	(i) Reasoning for treatment provided—based on historical context, literature sources, and traditional Chinese medicine (consensus) (ii) Reasoning for treatment provided—based on historical context, literature [27,28], selection of treatment regions based on related papers, expert experience, and textbooks
	(1c) Extent to which treatment varied	Standardized treatment
(2) Details of needling	(2a) Number of needle insertions per subject per session (mean and range where relevant)	10 or 12

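### A non-significant yes/no comparison at 20 to 24 per arm cannot show that blinding is sufficient, and the question is scheduled in week 4 in section 2.2 but in W1 in Table 1

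*Protocol article*

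**What the plan says.** Section 2.2 says that "participants will be asked to answer the following question during week 4 to test the blinding effect". The answer is 'yes' or 'no', and the percentage answering 'yes' "in both groups after the final treatment will be analyzed". The reading of a null result is then fixed in advance: "no significant difference in the response to this question between the two groups, they could suggest that the blinding effect is sufficient". No margin, interval or blinding index accompanies this.

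Section 2.9.1 supplies the test: "The level of significance is established at *α* < 0.05 with a two-tailed test", and "chi-square tests for categorical data". Section 2.6 plans 20 analysed and 24 recruited per group.

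In Table 1 the row "Assessment of blind method" has a single cross, in W1. It has none in W4.

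On the procedures, section 2.5.1 says for the acupoint arm that "EX-HN12 and EX-HN13 will be quickly inserted for bloodletting", and it also needles RN23 (called CV23 elsewhere). Section 2.5.2 says of the control arm: "Procedures and other treatment settings will be the same as in the acupoint group but with no needle manipulation for de qi". Its listed sites, there and in Table 5, are NA 1 to NA 3, near HT5, GB39 and ST8.

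**The concern.** Failing to find a difference is not evidence that there is none, least of all in a sample whose size was not derived for this comparison. The article's aim is to separate acupuncture from placebo, and its Discussion says efficacy could be confirmed if the acupoint arm proves superior to the control. That argument depends on participants in the two arms holding similar beliefs about what they received. A rule that often passes a 20-point gap gives little support for it.

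The schedule adds a second problem. A site that follows Table 1 collects the answer before most sessions have taken place, so the data would not describe belief at the end of treatment, which is what section 2.2 says will be analysed.

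**Working it through.** **Inputs.** From the article: 20 analysed and 24 recruited per group (section 2.6, 40 × 1.2 = 48 in total); 1:1 allocation (section 2.2); chi-square test, two-sided 0.05 (section 2.9.1); 3 sessions a week for 4 weeks, so 12 sessions (section 2.5). The article gives no expected 'yes' rates and no power for this test, so there is no stated figure to reproduce. The rates below are assumptions, shown over a range.

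**Chance of missing a real gap.** For each pair of true rates, sum the binomial probabilities of every pair of counts (a, b) for which the uncorrected Pearson chi-square gives p ≥ 0.05:

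P(miss) = Σ Bin(a; n, p1) × Bin(b; n, p2), over all (a, b) with p ≥ 0.05.

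| Assumed 'yes' rates | Gap (points) | Missed, 20 per arm | Missed, 24 per arm |
|---|---|---|---|
| 90 vs 70% | 20 | 64% | 57% |
| 80 vs 60% | 20 | 71% | 67% |
| 70 vs 50% | 20 | 75% | 69% |
| 90 vs 60% | 30 | 38% | 29% |
| 80 vs 50% | 30 | 47% | 39% |
| 90 vs 50% | 40 | 16% | 10% |
| 80 vs 40% | 40 | 25% | 16% |

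Rates centred on 50% do somewhat worse: 65 vs 35% is missed in 55% of trials at 20 per arm and 41% at 24. With Fisher's exact test at 20 per arm, the misses are 81% (80 vs 60%), 59% (80 vs 50%) and 35% (80 vs 40%).

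**One possible result.** Suppose 16/20 vs 11/20 answer 'yes'.
- Difference: 0.80 − 0.55 = 0.25. Pooled rate: 27/40 = 0.675.
- Chi-square: 0.25² / (0.675 × 0.325 × 2/20) = 2.85, p = 0.09.
- Wilson limits: 0.584 to 0.919 for 16/20, and 0.342 to 0.742 for 11/20.
- Newcombe lower limit: 0.25 − √[(0.80 − 0.584)² + (0.742 − 0.55)²] = −0.04.
- Newcombe upper limit: 0.25 + √[(0.919 − 0.80)² + (0.55 − 0.342)²] = 0.49.

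The rule would take this as a sign of sufficient blinding, although the data are compatible with a gap of nearly 50 points.

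**What showing similarity would need.** For two one-sided tests at 0.05 with 80% power, a true difference of zero and an assumed 20-point margin, n per arm = 2p(1 − p)(1.645 + 1.282)² / 0.20². This gives 69 at p = 0.8 and 108 at p = 0.5. At 20 to 24 per arm the approximate 95% half-width, 1.96 × √[2p(1 − p)/n], is 23 to 31 points over the same rates. The trial can estimate the gap, but it cannot show that the gap is small.

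**Timing.** The WAB row of Table 1 has crosses in W1, W4, W12 and W24, which confirms how the columns line up. The cross for the blinding question therefore stands in W1, when at most 3 of the 12 sessions have been given. Section 2.2 requires an answer in week 4, after the last session.

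**Procedures side by side.** The acupoint arm has sublingual bloodletting at EX-HN12 and EX-HN13 and a needle at CV23. The control arm lists three sham sites, none of them in the mouth or at the front of the neck. Section 2.5.2 nevertheless describes the procedures as the same except for de qi manipulation.

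**The case against.** A reader might infer that failed blinding would usually be declared a success. The documents do not support that. The test misses most 20-point gaps, but with the tabulated rates it detects a 30-point gap in 53 to 71% of trials and a 40-point gap in 75 to 90%. If the oral and neck procedures did give the allocation away, the gap could be large, and that is the case the test mostly catches.

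The wording is also cautious: the article says a null result could suggest sufficient blinding. It does not call it proof, and no trial decision or primary analysis depends on it. Section 2.2 adds real safeguards: an eye patch, separate treatment times, a ban on discussing the type of acupuncture, and emulation of the procedure in controls. Section 2.5.2 adds real needles and equal retention time. These reduce the risk, although an eye patch does not hide a prick under the tongue. The documents do not show that blinding will fail.

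A blinding index or an extra response option may properly be left to an analysis plan that is not shown, and their absence is not the point here. An analysis of the AQ effect by guess would be confounded, because a week-4 guess may reflect perceived benefit. The number of insertions should not be pressed either, since Table 3 gives 10 or 12.

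What remains is that the article itself states an interpretive rule, the only one it gives for this question, and the planned numbers cannot support it. The conflict between week 4 and W1 is not answered by any of this.

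**Conclusion.** The point holds in a limited form. At 20 to 24 per arm, non-significance cannot show sufficient blinding: a 20-point gap passes in about 57 to 75% of trials and a 30-point gap in about 29 to 47%, while gaps of 40 points or more are mostly found. These figures rest on the tabulated 'yes' rates, which are assumed, and on the uncorrected chi-square test. Fisher's test or rates nearer 50% would raise the misses, and the conclusion stands at either 20 or 24 per arm.

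The timing conflict is a plain contradiction and depends on no assumption. The description of the control procedures as otherwise the same is also inconsistent with the listed sites. It bears on how much weight the blinding check must carry, but it does not establish that participants will be unblinded.

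**What to change.** 1. In section 2.2, delete the sentence that infers sufficient blinding from a non-significant result. Replace it with: the percentage answering 'yes' after the final session will be reported by arm, with the between-arm difference and its 95% CI (Newcombe), and blinding will be judged from that interval. A per-arm blinding index with 95% CI is an optional addition.
2. Bring Table 1 into line with section 2.2, so that the answer is collected after the final session in week 4.
3. Reconcile the statement in section 2.5.2 that procedures are the same with the oral bloodletting and CV23 needling in section 2.5.1, which have no listed counterpart in the control arm. Which text is right is for the investigators to settle.

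The cost is a few sentences and one table cross, with no additional patients. The downside is that the trial can no longer claim adequate blinding from p > 0.05. With an interval of about ±23 to 31 points, it will often have to report that the question remains open.
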